#### Outcome 1: Adherence to evidence-based imaging guidelines.

The primary goal is to determine the impact of the CDSS on adherence to evidence-based imaging guidelines in terms of the appropriateness rates of imaging for cervical and lumbar spine X-rays.

For both groups (“Do nothing” and CDSS), we will compare pre-implementation data on the appropriateness of spine imaging referrals with post-implementation data of the same duration (2 months). Multiple readers will evaluate each clinical indication for appropriateness using the local set of diagnostic imaging referral guidelines, with disagreement resolved by consensus.

#### Outcome 2: Clinical effectiveness.

Addressing clinical effectiveness is critical to answering the question, “What is the impact of CDSS on patient outcome(s)?”. To assess the clinical effectiveness of CDSS in the real world, we will examine the clinically significant positive rates of imaging procedures performed, in tandem with the subsequent patient dispositions (i.e., treated and discharge, admission, referral to specialist, referral to physiotherapy and “At Own Risk”) at the end of the individual patient journey in the ED. The radiological reports of associated imaging procedures will be evaluated for significant positive findings that will impact therapeutic decisions, such as fractures in both the cervical and lumbar spines and soft tissue swelling in the cervical spine (i.e., fracture or prevertebral soft tissue swelling – sign of cervical spine jury, were considered positive; all else considered negative). To facilitate comparison in the proportions of positive findings among the categories, we will assess the imaging positivity rates in both the appropriate and inappropriate imaging cohorts. By using a longitudinal approach to monitor patients until their disposition, we will be able to clarify the risks physicians face regarding patient safety and quality of care, particularly in relation to the question: “What impact will following or not following imaging recommendations from the guidelines have on patient outcomes?” [41].

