**Fig 1 pone.0336801.g001:**
[figure not shown]
Flow chart and timeline of the study.

In the first phase for both groups, ED physicians will follow the usual clinical practice (“Do nothing”) of making imaging referrals without consulting CDSS. Both groups will be informed during their onboarding on the availability of imaging referral guidelines in the training handbook and also on the intranet. Specifically, the physicians in the control group will not receive any CDSS introduction/orientation and no additional imaging referral guidelines education beyond the standard onboarding process. Simultaneously, a retrospective analysis of the electronic medical records will be performed.

The study included consecutive patients referred to the ED’s radiology department for cervical and lumbar spine radiography by the cohort of recruited ED physicians. Patients who had imaging referrals from general practitioners will be omitted due to our lack of access to the clinical notes for this particular cohort. For each case, the initial clinical diagnosis (reasons for the referral), the ordered procedure, patient demographics (age and gender), and ED clinical notes will be collected. To enhance the accuracy of analysing each imaging referral, the initial clinical diagnosis will be integrated with the corresponding ED clinical notes, including signs, symptoms, clinical examination, and red flags. This integration will result in a more comprehensive “indication(s)” for the imaging procedure. The appropriateness of each imaging referral will be determined with reference to localised and institutional approved imaging referral guidelines built on imaging referral guidelines published by ACR, ESR and RCR (Refer to Table 1). The records will be archived to REDCap (Research Electronic Data Capture) hosted by SingHealth for subsequent analysis.

**Table 1 pone.0336801.t001:** Imaging referral guidelines* for X-ray Cervical and Lumbar Spine.

Procedure	Clinical condition	Appropriate Imaging Criteria

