Briefing slides and an introduction/orientation to the CDSS will be provided to ED physicians utilising the CDSS prior to the start of this second phase (Phase 2). The briefing slides will be curated by the vendor project manager and the principal investigator (PI) and subsequently be reviewed by the senior ED physicians for comprehensibility to ensure that the materials are well-defined and well-understood. Similarly, both the project manager and the PI will blueprint a 15-minute content plan for the introduction/orientation. The introduction/orientation will be conducted virtually by the research team members and the project manager assigned to the implementation. Topics covered include: (1) introduction to CDSS; (2) user workflow; (3) orientation of the CDSS input screen; (4) orientation of the CDSS guidelines screen; and (5) orientation of the CDSS recommendation screen. There will be no evaluation at the end of the introduction/orientation, but time will be dedicated for questions and answers. While no criteria for physician learning are available, it was deemed that the most effective learning for the time-constrained physicians was self-directed through the curated briefing slides, which will be disseminated through email and WhatsApp group.

The physicians will select pre-defined clinical history from the CDSS for imaging recommendations, and they will have the option to either follow or disregard them. We will study the referral practices of the recruited ED physicians in the intervention group over a consecutive period of two months. While ED physicians are not constricted by guidelines, during the study’s second phase, there will be special strategies to improve compliance and to motivate the physicians to adhere to the guidelines. This includes email reminders and the emphasis on the audit process.

The evaluation process in Phase 2 will mimic the pre-implementation evaluation process (Phase 1) to ensure comparable results and data. Essentially, we want to conduct a careful review of the difference between the baseline and post-implementation results. The analysis will include all participating physicians in an intention-to-treat fashion.

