#### Outcome 4: Radiation dose.

The established literature “Radiology: Patient Exposure from Radiologic and Nuclear Medicine Procedures in the United States: Procedure Volume and Effective Dose for the Period 2006–2016” will serve as the basis for estimating the radiation dose to patients [42]. The publication, based on the International Commission on Radiological Protection (ICRP) Publication 60, indicates an effective dose per scan of 0.36 mSv for X-rays of the Cervical Spine and 1.4 mSv for the Lumbar Spine. We will establish the cumulative effective dose associated with the imaging tests and highlight the comparison of the relative contributions of appropriate and inappropriate imaging with the total number of examinations and the total collective effective dose. We will also evaluate the number of imaging tests avoided (i.e., physician after consulting CDSS followed CDSS recommendations on not referring patient(s) for imaging) and the associated radiation dose prevented using the formula: “effective dose per scan X number of imaging avoided”.

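### Outcome 2 promises a patient-safety answer, but it observes only X-rayed patients up to ED disposition, so missed injury after an X-ray withheld on CDSS advice is not directly observable

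*Protocol article*

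**What the plan says.** **Population.** Under Comparator and intervention, the protocol article describes the dataset: "The study included consecutive patients referred to the ED" and, continuing the same sentence, "radiology department for cervical and lumbar spine radiography by the cohort of recruited ED physicians". For the second phase it adds: "The evaluation process in Phase 2 will mimic the pre-implementation evaluation process (Phase 1) to ensure comparable results and data".

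**Measure.** Under Outcome 2, "we will examine the clinically significant positive rates of imaging procedures performed", together with each patient's disposition. Positive findings are read from the radiology reports, and positivity is compared between appropriate and inappropriate imaging. Patients are followed until they leave the ED.

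**Claim.** The same section says this will clarify patient-safety risk and address the question "What impact will following or not following imaging recommendations from the guidelines have on patient outcomes".

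**Avoided X-rays.** Under Outcome 4, "We will also evaluate the number of imaging tests avoided", defined as cases in which the physician consulted the CDSS and followed its advice not to refer. Outcomes 4 and 5 multiply that number by dose, energy and carbon per examination.

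**Scoring rule.** Outcome 2 introduces significant findings by way of example, naming fractures and cervical soft tissue swelling. The bracket that follows is exhaustive: fracture or prevertebral swelling "were considered positive; all else considered negative".

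**The concern.** Advice not to image can harm a patient through a lesion that is then not found. The patients exposed to that risk are those in whom the advice was followed. They have no referral and no radiology report, so they belong to neither the appropriate nor the inappropriate imaging cohort. The question the section poses has two sides, following and not following, and for advice against imaging the following side is absent from the data.

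The end of observation adds to this. An injury missed in the ED would usually show as a return visit, later imaging or a later diagnosis, and nothing is collected after disposition.

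At stake is what the trial may conclude. The saving from withheld X-rays is credited in dose, energy and carbon, while Outcome 2 is the only outcome presented as addressing patient safety. A favourable result there could be reported as evidence that withholding was safe, which the data would not show.

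The scoring rule is a separate matter. If a film confirms malignancy or infection without fracture, it counts as negative even though suspicion of that disease is what made the referral appropriate.

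**Working it through.** **1. Who is observed.** The point rests on ascertainment, so the groups are set side by side.

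| Patient group | In dataset? | Radiology report? | Disposition? | Anything after ED? |
|---|---|---|---|---|
| Referred, appropriate | yes | yes | yes | no |
| Referred, inappropriate (no CDSS in that phase, or CDSS not consulted or overridden) | yes | yes | yes | no |
| X-ray withheld on CDSS advice | number only (Outcomes 4 and 5) | no | none described | no |

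A withheld patient who came back and was referred by a recruited physician within the window could enter as a new referral, but no linkage to the index visit is described.

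**2. Scale.** The article gives neither the number withheld nor any positivity rate. The only figures available are 235 per group and 20% inappropriate, from Sample size. The 235 reproduces: 2 × (1.960 + 1.282)² / 0.3² gives 234, and the exact two-sample t-test gives 234.46, so 235. It serves here only as a scale: 235 × 0.20 = 47 inappropriate and 188 appropriate films.

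**3. Can positivity rise while lesions are missed?** Assume 8% positivity in appropriate films and a rate q in inappropriate ones, with all 47 withheld. Positivity before is (188 × 0.08 + 47q)/235; after, it is 188 × 0.08/188 = 8.0%.

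- q = 1%: (15.04 + 0.47)/235 = 6.6%, rising to 8.0%; 0.47 lesions unimaged.
- q = 3%: (15.04 + 1.41)/235 = 7.0%, rising to 8.0%; 1.41 lesions unimaged.
- q = 10%: (15.04 + 4.70)/235 = 8.4%, falling to 8.0%; 4.70 lesions unimaged.

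Positivity rises only if the withheld films have a lower lesion rate than the rest. A rise is therefore informative about relative yield, but it does not mean that no lesion was missed.

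**4. Range of expected misses.** If 25% to 100% of the 47 are withheld (about 12 to 47 patients) and 0.5% to 5% of them carry a lesion, expected misses run from 11.75 × 0.005 = 0.06 to 47 × 0.05 = 2.35. The chance of at least one, 1 − (1 − q)ⁿ, runs from about 6% to 91%. All of these inputs are assumptions.

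**5. What follow-up could show.** With zero events in n patients, the one-sided 95% upper limit is 1 − 0.05^(1/n), or roughly 3/n. For an assumed n = 25 this is 11.3% (3/25 = 12%); for n = 50, 5.8% (3/50 = 6%). Follow-up makes harm observable but does not exclude a rare harm.

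**6. Scoring rule.** Table 1 accepts suspected metastatic disease (lumbar) and suspected infection (lumbar, and non-traumatic neck pain) as appropriate indications. On the 188-film scale, each appropriate film that shows malignancy or infection without fracture or swelling and is scored negative lowers measured yield in that cohort by 1/188 = 0.5 percentage points. The documents do not give the number of such films.

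**The case against.** A reader might infer that Outcome 2 can only favour the CDSS or be neutral. The documents do not support that. Positivity is compared between appropriate and inappropriate films, and a high rate among inappropriate films would count against the guideline. In three of the four group-phases (Phase 1 of both groups and Phase 2 of the control group) no CDSS is in use, so guideline-negative patients whom these physicians chose to refer were X-rayed and have a report. That is real evidence on what following the advice might miss. It stays indirect, because those patients may differ from the ones in whom the CDSS actually stops an X-ray. The Discussion also cites earlier local work on this question, but that is not an observation of this trial's withheld patients.

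Nor does a rise in positivity look the same whatever was withheld: step 3 shows that it falls when the withheld films carry more lesions than the rest. And the scoring rule lowers yield in the appropriate cohort, so it tends to work against the guideline rather than for it.

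Three further objections stand in part. Table 1 lists reasons for referral, not target radiographic findings, so an outcome definition need not mirror it; what remains is that the wording by example and the exhaustive rule within Outcome 2 do not agree, and that the rule leaves out diseases which Table 1 accepts as reasons to image. The CDSS is standalone, and no link from its use to patient records is described, so a look-up may not be possible for every avoided case. No comparable non-imaged group exists in Phase 1 or in the control group, so any such count would be uncontrolled.

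**Conclusion.** The point holds in a limited form. The article itself fixes the population, the data source and the end of observation, so this is not a detail left to an unseen plan. Under them, missed injury in patients whose X-ray was withheld on CDSS advice cannot be observed directly, and the claim to show what following recommendations does to patient outcomes goes beyond the design. Positivity of inappropriate films is indirect evidence on misses; a rise in positivity after CDSS does not exclude them.

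The size is not knowable from the documents. On assumed inputs, expected misses are 0.06 to 2.35 per 235 referrals, none of which the plan would link to the withheld X-ray.

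The scoring rule is a smaller inconsistency that can understate yield in the appropriate cohort. The primary outcome, appropriateness, is untouched by either point.

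**What to change.** 1. **Restrict the Outcome 2 conclusion** to diagnostic yield and ED disposition among imaged patients, and label positivity of inappropriate films as indirect evidence on missed lesions. This is a change of wording and costs nothing.

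2. **Where the avoided cases counted under Outcome 4 can be linked to the hospital record**, also report their ED re-attendance, later spine imaging and spine diagnosis within a fixed, prespecified window (for example 30 days), as an uncontrolled count with an exact upper limit. Costs: linkage work, returns to other hospitals missed, and a possible ethics notification. The report should say that zero events in a few dozen patients leaves a wide bound. If linkage is not possible, item 1 stands alone.

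3. **Reconcile the positivity definition.** Either count radiographic findings of malignancy or infection as positive, or keep the present rule and report the result as fracture and soft-tissue-injury yield only. The first option means coding additional findings from reports already being read; the second is a relabelling.

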X-ray Cervical Spine	Acute trauma	1. Patient age is > 65 years old 2. Patient GCS score <15 3. Patient is intoxicated 4. Patient has midline spinal tenderness 5. Presence of focal neurological deficit 6. Presence of paraesthesia in extremities 7. Patient is unable to actively rotate neck left and right to 45 degrees 8. Not possible to test range of neck movement during patient assessment 9. Presence of dangerous mechanism of injury – fall from >1 meter/5 stairs 10. Presence of dangerous mechanism of injury – axial load injury 11. Presence of dangerous mechanism of injury – high speed motor vehicle accident 12. Presence of dangerous mechanism of injury – rollover motor vehicle accident 13. Presence of dangerous mechanism of injury – motor vehicle accident with ejection 14. Presence of dangerous mechanism of injury – motorised recreational vehicles 15. Presence of dangerous mechanism of injury – bicycle collisions
	Non-traumatic neck pain	1. Patient has history and/or current malignancy 2. Patient has prior cervical spine surgery 3. Presence of symptoms for spinal cord injury 4. Patient is suspected to have an infection 5. Patient has history of IV drug use 6. Patient has systemic disease including spondyloarthritis and diffuse idiopathic skeletal hyperostosis 7. Presence of intractable pain despite therapy 8. Patient has tenderness to palpation over a vertebral body 9. Presence of neurological deficits 10. Presence of radiculopathy 11. Presence of neck pain
X-ray Lumbar Spine	Low back pain (LBP)	1. Patient age is > 65 years old 2. Patient is osteoporotic 3. Patient has chronic steroid use 4. Patient has low velocity trauma 5. Patient is suspected to have metastatic disease 6. Patient is suspected to have an infection 7. Patient is immunosuppressed 8. Patient is a surgical candidate with persistent or progressive symptoms during or following 6 weeks of conservative management 9. Patient has prior lumbar surgery with new or progressive symptoms or clinical findings 10. Patient has trauma of dangerous mechanism

*Approved by Institution’s Medical Board.

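### Outcome 2 sets out to count findings that change treatment, but its coding rule counts only fracture or prevertebral swelling, which does not fit the non-traumatic indications in Table 1

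*Protocol article*

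**What the plan says.** The protocol article, Outcome 2: Clinical effectiveness, has radiology reports read for "significant positive findings that will impact therapeutic decisions, such as fractures in both the cervical and lumbar spines", and adds soft tissue swelling for the cervical spine. A bracket opening with i.e. then turns this into a coding rule: fracture or prevertebral swelling is a "sign of cervical spine jury, were considered positive; all else considered negative".

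The resulting rate is used to compare cohorts: "we will assess the imaging positivity rates in both the appropriate and inappropriate imaging cohorts". It is examined together with each patient's disposition on leaving the ED. The stated purpose is to learn what following or ignoring the guideline recommendations means for patients.

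Table 1 sets out what makes a film appropriate, and it is not confined to trauma. The lumbar list includes "Patient is suspected to have metastatic disease 6. Patient is suspected to have an infection 7. Patient is immunosuppressed", and also prior surgery with new or worsening features. The list for non-traumatic neck pain includes "Patient has history and/or current malignancy", prior cervical surgery, and "Patient is suspected to have an infection 5. Patient has history of IV drug use".

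**The concern.** The sentence gives an open concept (findings that matter for treatment, with fracture as an example) and then a closed rule (two findings, everything else negative). A person coding reports has to apply the closed rule, and nothing else in the article widens it.

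The closed rule suits trauma. Table 1 also sends films for tumour, infection and post-surgical problems, and the rule has no category for what those films look for. The study can therefore call a film appropriate because metastasis is suspected, and then record it as negative when it shows a destructive lesion without a fracture.

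At stake is the comparison of yield between appropriate and inappropriate films, which is the article's evidence on whether the guidelines are safe to follow. The Discussion says earlier work met physicians' concerns about effectiveness and risk in both traumatic and non-traumatic patients. For the non-traumatic group, an endpoint limited to fracture and swelling is a weak test.

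**Working it through.** The plan gives no positivity rate, so there is no figure of its own to reproduce. The check sets the texts side by side and then asks what the mismatch does to the comparison.

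**1. Concept against rule (Outcome 2).**
- Concept: "significant positive findings that will impact therapeutic decisions", with fracture introduced as an example.
- Rule: fracture or prevertebral swelling "were considered positive; all else considered negative".
- A treatment-changing finding that is neither of these is positive under the concept and negative under the rule. The swelling clause is cervical, so for lumbar films only fracture counts.

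**2. Rule against indications (Table 1).**

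| List | Indications aimed mainly at something other than fracture | Items |
|---|---|---|
| Lumbar, low back pain (10 items) | suspected metastasis, infection, immunosuppression, surgical candidate, prior surgery | 5–9 |
| Cervical, non-traumatic (11 items) | malignancy, prior surgery, infection, IV drug use, systemic disease | 1, 2, 4, 5, 6 |

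That is 5 of 10 and 5 of 11 items. These are counts of list entries, not of referrals or findings. They show that the mismatch is not confined to one stray criterion, and they say nothing about its frequency.

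**3. Effect on the comparison.** Let f be the rate of fracture or swelling and u the rate of other treatment-changing findings, with A for appropriate and I for inappropriate films.
- Recorded difference = f_A − f_I
- Full difference = (f_A + u_A) − (f_I + u_I)
- Recorded minus full = u_I − u_A

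If u_A exceeds u_I, the recorded contrast is too small. If u_I exceeds u_A, it is too large. Films with the indications in step 2 are appropriate by definition, so u_A may well be the larger, but the documents give neither rate. Whatever the net effect, every case counted in u_I is a finding in a film the guidelines would not have supported, and the rule hides it.

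**4. Where u_I can arise.** Item 11 of the non-traumatic cervical list is simply the presence of neck pain, so nearly every such film is appropriate and the inappropriate group is almost empty. On the lumbar side, suspected metastasis and suspected infection are themselves appropriate criteria. What remains is mainly unsuspected lumbar disease.

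**5. Illustration on assumed rates only.** Share of significant findings missed = u / (f + u).

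| f (assumed) | u (assumed) | Recorded | All significant | Share missed |
|---|---|---|---|---|
| 5% | 1% | 5% | 6% | 1/6 = 17% |
| 5% | 5% | 5% | 10% | 5/10 = 50% |
| 10% | 0.2% | 10% | 10.2% | 0.2/10.2 = 2% |
| 10% | 1% | 10% | 11% | 1/11 = 9% |
| 10% | 5% | 10% | 15% | 5/15 = 33% |

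The range of 2% to 50% follows from the assumed inputs and is not an estimate for this study.

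**The case against.** The strongest defence is textual. The main clause is open, and the bracket follows directly on the cervical finding and speaks of cervical injury, so it might define the cervical element only and leave lumbar positivity open. This is a strained reading, because the bracket names fracture, which the sentence has just given for both regions, and then excludes everything else. Even if it were right, two coders could classify the same lumbar report differently, and the sentence would still need repair.

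Second, Outcome 2 also records disposition. A tumour or infection that changed management could show up as an admission or a specialist referral. That partly complements the positivity rate, but it does not correct it.

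Third, a closed definition is reproducible between readers. This stands, and it is why any wider definition needs a list fixed beforehand.

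Several stronger readings are tempting, and the documents do not support them:
- *All tumour and infection findings are lost.* They are not. A pathological fracture, or a cervical infection with prevertebral swelling, still counts as positive. Table 1 also lists reasons for imaging, not radiological results.
- *The bias runs one way.* It does not, because the two errors oppose each other in the contrast (step 3 of the working).
- *A substantial, known share of positives is lost.* No rate is given. The recruited physicians work mostly with ambulant minor and non-emergency cases, where other treatment-changing findings may be rare.
- *The question about following the guidelines gets a wrong answer outside trauma.* The text supports only that the answer can be biased.

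**Conclusion.** The point holds as an inconsistency in the definition of one component of an associated outcome. The coding rule does not match the lead-in of its own sentence or the non-traumatic indications in Table 1. Applied as written, it codes as negative any treatment-changing tumour, infection or post-surgical finding that comes without fracture or prevertebral swelling.

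This can lower recorded positivity in the appropriate cohort and can conceal unsuspected disease in the inappropriate cohort, the latter mainly in lumbar films. The net direction and the size cannot be determined from the documents. The conclusion assumes only that coders follow the bracketed rule as the operative one.

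The appropriateness outcome, its analysis and the sample size do not depend on positivity and are not affected.

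**What to change.** Reconcile the sentence. Define a positive film as one with any reported finding that would affect treatment for its Table 1 indication. Have the study's radiologists and ED physicians fix the list of qualifying findings before reports are coded. The list should cover at least tumour, infection and post-surgical findings, alongside fracture and cervical prevertebral swelling.

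Keep the fracture-or-swelling definition as a secondary measure, so that results remain comparable with any earlier work that used it. Report both definitions separately for trauma and non-trauma referrals and for cervical and lumbar films, so that readers can see where they diverge.

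The cost is one revised definition and a few extra fields when reading reports that are already being reviewed. Coding becomes slightly heavier and readers need a little more agreement beforehand.
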